## Abstract

**Background:**

There are a growing number of mHealth tools for breast cancer patients but a lack of scientific evidence for their effects. Recent studies have shown a mix of positive and negative impacts on users. Here we will assess the impact of OWise Breast Cancer, a mobile application for self-monitoring symptoms and managing care, on the process of self-management.

**Methods:**

This randomized controlled trial with early stage breast cancer patients will assess the effect of OWise use on patient activation at 3 months from diagnosis measured by the PAM-13 questionnaire. We will also assess differences in changes in health-related quality of life, psychological distress, health status, and National Health Service (NHS) health resource utilization over the first year from diagnosis. Participants will be randomly allocated (1:1) to standard care or standard care plus OWise. Participants will complete questionnaires before starting anti-cancer treatment and at 3, 6, and 12 months from diagnosis. Clinical and patient-reported outcome data will be linked to health resource utilization data from Discover, an integrated care record of primary, secondary, and social care in North West London. We will measure contamination in the control group and adjust the sample size to mitigate the dilution of effect estimates. A per-protocol analysis will be conducted as a sensitivity analysis to assess robustness of the primary results.

**Discussion:**

This study aims to generate evidence for the effectiveness of OWise at improving patient activation for women with early-stage breast cancer. The results will show the impact of using the tool at the patient level and the NHS health system level. The outcomes of the study will have implications for the application of OWise across the NHS for breast cancer patients and expansion into other tumor types. Assessing publicly available mHealth tools poses a challenge to trialists due to the risk of contamination. Here we apply various methods to measure, mitigate, and assess the effects of contamination.

**Trial registration:**

The study was registered at clincaltrials.gov (NCT03866655) on 7 March 2019.

## Background

Breast cancer is the most common form of cancer diagnosed in the United Kingdom (UK), with around 55,200 new cases each year [1]. In 2010, the National Health Service (NHS) in England spent around £675 million for the care of patients with breast cancer, with current NHS and broader societal costs likely exceeding this value [2]. With the incidence of breast cancer expected to increase in the UK over the next 15 years [1], the NHS is promoting increased self-management of care [3].

Patients and providers are looking to mHealth applications for potential self-management benefit in cancer populations [4]. mHealth is the application of mobile technology by patients or health care providers to monitor health and improve outcomes [5]. A recent review has found 12 studies assessing mHealth tools to support self-management in breast cancer patients [6]. Many of the studies assessing mHealth tools found promising results with a wound monitoring application reducing health resource utilization [7], an electronic daily journal stabilizing daily functional activity [8] and an application providing information and support improving self-efficacy and quality of life and reducing symptom interference [9]. However, one application providing tailored information before surgery increased levels of anxiety and depression in patients [10]. The inconsistency in effects highlights the need to rigorously assess the impact of mHealth tools before encouraging use.

OWise Breast Cancer is a new mHealth technology for the self-management of care in breast cancer patients. OWise provides tailored medical information, a tracker to self-monitor symptoms and functions to manage care including an appointment calendar, modifiable question list and consultation recording device [11]. OWise, listed in the NHS Apps Library, is freely available for download [12]. OWise was developed outside an academic setting but followed the mHealth development and evaluation process defined by Whittaker et al. [13]. Programmers designed the tool in an iterative process with patients and conducted thorough user testing.

A qualitative study evaluating OWise in the Netherlands showed patients and providers found the tool usable and felt it had the potential to help patients take in more information from consultations, manage appointments, and feel more in control during treatment [14]. To understand the impact of OWise on health behaviors, health-related quality of life (HRQoL), and NHS resource utilization, comparative data are needed.

### Conceptual model

The conceptual model for OWise is based on the Individual and Family Self-Management Theory. This theory posits that self-management is the process by which individual and family health knowledge and behaviors are used to reach certain health outcomes (Fig. 1) [15]. The theory takes into account individual, medical, social, and environmental factors that influence the process of self-management.

**Fig. 1 Fig1:**
[figure not shown]
The Individual and Family Self-Management Theory

OWise aims to improve HRQoL and reduce health resource utilization by intervening on the self-management process. The digital tool aims to increase knowledge and beliefs by providing tailored medical information and recommended questions in the modifiable question list. OWise aims to improve self-regulation skills and abilities with the symptom tracker and appointment calendar. The proximal outcome we will measure is patient activation and distal outcomes are HRQoL, psychological distress, health status, and health care costs. Studies have previously linked patients’ activation to better HRQoL, improved care experiences, and lower use of NHS resources [16–18].

## Methods

### Aim

This study aims to understand the impact of OWise on health behaviors, HRQoL, and health care utilization in early stage breast cancer patients compared to standard care alone.

### Study design

We will evaluate the effectiveness of OWise using a multi-center, individually randomized, parallel controlled trial recruiting 122 patients. The intervention group will receive OWise plus standard care, while the control group will receive standard care alone to assess superiority. Due to the nature of the digital tool, it is not possible to blind participants or providers. Outcomes are reported directly by participants and analysis depends on the randomly assigned group. Therefore, outcome assessors and data analysts are not blinded either. Patients in both groups will complete patient-reported outcome measures (PROMs) to assess outcomes at baseline, 3, 6, and 12 months from diagnosis. See Fig. 2 for the SPIRIT diagram showing the schedule of enrolment and assessment and Additional file 1 for the SPIRIT checklist.

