### Participants

Females (aged 18 years or over) newly diagnosed with early stage breast cancer as a first primary diagnosis will be eligible to take part. Eligibility was restricted to early stage and first primary diagnoses as metastatic patients may have confounding care and psychosocial experiences and patient activation naturally increases with time after a breast cancer diagnosis [22]. Patients must complete the baseline measure before starting anti-cancer treatment. All participating sites are located in the UK, a list of which can be found on the registration website. Exclusion criteria include private care, difficulty reading in English, significant cognitive impairments or poor mental health, and no Internet access.

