### Primary objective

The primary objective of this study is to test whether the use of OWise increases patient activation scores at 3-month follow-up by at least four points more than standard care.

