### Procedure

#### Recruitment

We will continuously sample all patients meeting eligibility criteria diagnosed within the recruitment period. A member of the clinical team will identify eligible patients in multi-disciplinary team meetings or clinic lists and invite potential participants at diagnosis. The name of the digital tool will not be disclosed when inviting patients. If a patient shows interest, a researcher will provide further information either in person or over the phone. Patients can decide to take part any time before starting anti-cancer treatment.

After meeting eligibility criteria and providing written informed consent, participants will be randomized. The researcher will inform the participant of their allocation and provide instructions for accessing the online PROM collection tool. Participants in the intervention arm will be required to complete the baseline measure before using OWise.

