##### Health care utilization

Health care utilization will be assessed using data routinely collected in Discover. The Discover-linked dataset includes coded information on health and social care resource utilization of individuals registered with a GP practice in the North West London region. Information is collected about the number and type of appointments from primary, secondary, and social care for each patient between diagnosis and 1-year follow-up.

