### Sample size

Sample size calculations are based on the change in PAM-13 score from baseline to 3 months. A difference of four points is considered clinically relevant [29, 45]. In a similar study, the mean PAM-13 score at baseline for the intervention group was 61.3 (SD 16.61) and 67.9 (SD 16.85) at 3 months [46]. For the control group, the study reported a mean PAM-13 score at baseline of 62.1 (SD 17.30) and 62.8 (SD 14.94) at 3 months. Based on these findings, this study is planned to detect a mean change difference of 5.90 assuming a common standard deviation of 10.0. Using an 80% power, the study will recruit 47 patients per group. This was calculated using a two-sided test with alpha = 0.05. We will increase the sample size taking 23% attrition at 3 months into account (47/(1–0.23)) to 61 patients per group [47] and, as mentioned above, increase the sample size accordingly if contamination is found near the end of recruitment.

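### Outcomes are clocked from diagnosis but patients are randomized after an uncapped gap, so OWise exposure varies and resource use before randomization enters the outcome

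*Protocol article*

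**What the plan says.** **Questionnaires.** Study design schedules them "at baseline, 3, 6, and 12 months from diagnosis". The abstract defines the primary outcome as "patient activation at 3 months from diagnosis measured by the PAM-13 questionnaire". The Primary objective speaks of whether OWise "increases patient activation scores at 3-month follow-up by at least four points more than standard care", without naming the origin of the 3 months.

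**Entry and start of OWise.** Under Recruitment, patients are invited at diagnosis, and "Patients can decide to take part any time before starting anti-cancer treatment". Then: "After meeting eligibility criteria and providing written informed consent, participants will be randomized". The intervention arm must complete the baseline questionnaire before using the tool. The article states no maximum gap between diagnosis and randomization.

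**Resource use and cost.** Health care utilization collects contacts "for each patient between diagnosis and 1-year follow-up". The Secondary objectives put both utilization and cost on the same clock, the first year after diagnosis.

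**Planning basis.** Under Sample size, "Sample size calculations are based on the change in PAM-13 score from baseline to 3 months".

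**Time trend.** Participants states that "patient activation naturally increases with time after a breast cancer diagnosis".

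**The concern.** Three dates are in play: diagnosis, randomization (closely followed by baseline and, in one arm, OWise) and the outcome date. The outcome date is tied to the first, while the intervention starts after the second. This has two consequences.

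First, exposure at the primary time point is 3 months minus a gap that differs from patient to patient. The PAM-13 change covers the same shortened, variable interval. By the article's own account activation rises after diagnosis, so a floating baseline date adds variation to the change score. If the effect of OWise takes time to build, a long gap would also weaken it.

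Second, contacts and costs between diagnosis and randomization are part of a randomized outcome although allocation cannot influence them. They bring variance and no information about OWise, and the window gives up an equal amount of time after randomization at its far end.

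**Working it through.** **1. The plan's own figure.** Inputs from Sample size: the similar study's intervention arm went from 61.3 to 67.9 (+6.6) and its control arm from 62.1 to 62.8 (+0.7), so the difference is 6.6 − 0.7 = 5.9. SD is 10.0, alpha 0.05 two-sided, power 80%.
- Normal approximation: n = 2 × (1.960 + 0.842)² × 10² / 5.9² = 45.1, so 46 per arm.
- t test with d = 0.59: 46.08, so 47 per arm, as stated. Power with 47 is 80.8%.
- Attrition: 47 / (1 − 0.23) = 61.04, stated as 61.

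The figure reproduces, and it does not depend on which clock is used.

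**2. Exposure and an illustration of dilution.** The article does not give the gap g, so a range is assumed. Exposure is 91 − g days. As a second assumption, let the effect be proportional to exposure: effect = 5.9 × (91 − g) / 91. Power is for a t test with 47 per arm and SD 10.

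| Gap g (days, assumed) | Exposure (days) | Effect if proportional | Power | n per arm for 80% | g / 365 |
|---|---|---|---|---|---|
| 0 | 91 | 5.90 | 81% | 47 | 0% |
| 7 | 84 | 5.45 | 74% | 54 | 1.9% |
| 14 | 77 | 4.99 | 67% | 64 | 3.8% |
| 21 | 70 | 4.54 | 59% | 78 | 5.8% |
| 31 | 60 | 3.89 | 46% | 105 | 8.5% |

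If the effect is immediate, the first row applies whatever the gap.

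**3. Noise from the floating baseline.** If activation drifts by b points per day, two patients whose gaps differ by k days differ in expected change by b × k. The only drift figure in the article is the similar study's control arm, 0.7 points over 3 months. At that rate a 31-day difference is worth 0.7 × 31 / 91 = 0.24 points, small against an SD of 10. The article does not say whether the rise is steeper just after diagnosis.

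**4. Resource use.** Write a patient's total as Y = A + B, with A before and B after randomization.
- Difference in means: E(Y, OWise) − E(Y, control) = E(B, OWise) − E(B, control), because A has the same expectation in both arms. Including A does not shrink the difference.
- Variance: Var(Y) = Var(A) + Var(B) + 2 Cov(A, B), which exceeds Var(B) unless A and B are sufficiently negatively correlated.
- Window: B covers only 365 − g days, that is 358 to 334 days for gaps of 7 to 31 days.

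Secondary endpoints compares mean rate and mean cost by linear regression, so the difference in means is the relevant measure.

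**The case against.** Diagnosis is used consistently as the origin, and there is a sensible reason for it. Because activation changes with time since diagnosis, this anchor places every patient at the same point on that path when the outcome is measured. Re-timing the questionnaires from randomization would let time since diagnosis vary at each assessment. It would also let treatment stage vary, which matters for the quality-of-life, distress and health-status measures. This stands, and it makes re-timing a trade-off rather than a correction.

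A reader might infer that patients get less exposure than planned and that the trial is therefore underpowered. The documents do not support that. No exposure period is fixed anywhere. The interval under Sample size can be read as the change between two scheduled assessments, the second of them at 3 months from diagnosis. The article does not say from what date the similar study counted its 3 months. Patients are invited at diagnosis, so gaps may be short, and functions such as the tailored information, question list and consultation recorder could act early.

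A reader might also infer that early contacts shrink the resource effect. That would be true of a relative reduction, but the plan compares means. First-year cost from diagnosis is also a legitimate quantity for the NHS.

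Finally, the schedule figure is not shown, and the full protocol may set a maximum gap. What remains is that the clock stated in the article leaves the gap open and counts contacts before randomization.

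**Conclusion.** The point holds as one of precision and interpretation. Exposure to OWise and the interval behind the PAM-13 change vary between patients by an amount that is neither given nor capped in the article, and the utilization and cost outcomes contain a stretch that OWise cannot affect. The gap from diagnosis to randomization precedes allocation, so the arms are balanced on it in expectation and there is no bias between them.

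The size is unknown. The drop in power from 81% to between 74% and 46% needs both an assumed gap of 7 to 31 days and an effect proportional to exposure; it is illustrative and not a finding that the trial is underpowered. Noise in PAM-13 from the floating baseline may be small. For resource use, 1.9% to 8.5% of the year by calendar time would precede randomization under the same assumed gaps. The share of contacts could differ if they cluster after diagnosis, which the article does not say. The effect on the planned difference in means is added variance, plus the loss of an equal stretch of follow-up at the end of the window.

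**What to change.** 1. **Discover outcomes.** Count use and cost for 12 months from randomization. Enter use and cost between diagnosis and randomization as a baseline covariate in the corresponding models. Keep first-year-from-diagnosis totals as a descriptive NHS-level summary.
2. **PAM-13 regression model.** Include days from diagnosis to baseline as a prespecified covariate, whatever the univariate screen at p < 0.1 shows. This can reduce noise; it does not restore lost exposure, and it leaves the planned t test as it is.
3. **Reporting.** Give the distribution of the gap by arm, split at randomization. Under Recruitment, patients learn their allocation before they are given access to the questionnaires, so the part from randomization to baseline is not protected by randomization.
4. **Option for the sponsor to weigh.** Time the questionnaires from randomization, accepting that time since diagnosis and treatment stage would then vary at each assessment.

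The cost of items 1 to 3 is a slightly later data cut for Discover and one extra covariate per model. The stated sample size need not change. Trial status describes recruitment as pending, so these choices can be fixed before any data exist.

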**Fig. 2 Fig2:**
[figure not shown]
Schedule of enrolment and assessments

### Randomization

Patients will be randomly assigned (1:1) to the intervention or control group [19, 20]. Randomization will be stratified by age group and center. Age is grouped by (1) under 60 years old and (2) 60 years old and over as internet access drops between age groups 45–55 and 55–65 [21] and the incidence of breast cancer in the UK is evenly distributed around age 60 [1]. The Institute of Cancer Research Clinical Trials and Statistics Unit Randomisation Service will generate the randomization sequence and allocate the group by phone.

### Participants

Females (aged 18 years or over) newly diagnosed with early stage breast cancer as a first primary diagnosis will be eligible to take part. Eligibility was restricted to early stage and first primary diagnoses as metastatic patients may have confounding care and psychosocial experiences and patient activation naturally increases with time after a breast cancer diagnosis [22]. Patients must complete the baseline measure before starting anti-cancer treatment. All participating sites are located in the UK, a list of which can be found on the registration website. Exclusion criteria include private care, difficulty reading in English, significant cognitive impairments or poor mental health, and no Internet access.

### Intervention group

OWise is an mHealth tool accessible online or by mobile application [11]. The tool offers tailored medical information, a modifiable question list with tailored recommended questions, a medical terms glossary, useful links to local resources, and a tracking tool for symptoms, an appointment calendar, and a consultation recording device.

In the study, only patients randomized into the intervention group will receive information about OWise. The individual enrolling the patient will provide instructions for creating an account and navigating the tool. Participants will be free to use the tool as much as they wish to mimic real-world use of the application. The tool is free to download and accessible to the participant beyond the study period.

### Control group

Participants in the control group will receive all standard information including leaflets and links to resources that patients usually receive at the time of a new breast cancer diagnosis. Participants in the control group will not be given information about the tool but will also not be explicitly prohibited from using the tool.

### Primary objective

The primary objective of this study is to test whether the use of OWise increases patient activation scores at 3-month follow-up by at least four points more than standard care.

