#### Primary endpoint

We will compare the PAM-13 score change between the intervention arm and the control arm using independent *t* test. Data will be log-transformed to achieve normality as appropriate. We will also compare the mean change in PAM-13 score in the intervention and control arm in a multiple linear regression model including potential covariates.

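### The primary objective is a benefit of at least four PAM-13 points, but the planned test and sample size are for superiority over zero, so p < 0.05 alone would not show that the objective is met

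*Protocol article*

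**What the plan says.** All references are to the protocol article.

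- **Primary objective:** the aim is "to test whether the use of OWise increases patient activation scores at 3-month follow-up by at least four points more than standard care". The four points are part of the proposition to be tested.
- **Study design:** the comparison with standard care is described as one of superiority. No margin is given.
- **Analysis, Primary endpoint:** "We will compare the PAM-13 score change between the intervention arm and the control arm using independent" t test. No null value other than zero is named. The general Analysis section sets two-sided significance at p < 0.05.
- **Sample size:** "A difference of four points is considered clinically relevant", but "this study is planned to detect a mean change difference of 5.90 assuming a common standard deviation of 10.0". Then: "Using an 80% power, the study will recruit 47 patients per group", and "This was calculated using a two-sided test with alpha = 0.05". Attrition of 23% raises this to 61 per group, 122 in total.

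No section sets a null of four points or a rule for reading a confidence limit against four points.

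**The concern.** The objective and the test answer different questions. A t test against zero asks whether the mean changes differ at all. The objective asks whether they differ by four points or more. If the result is significant, the protocol as written offers nothing further to decide whether its primary objective has been met, and the obvious reading is that it has. Yet the data could be compatible with a true benefit well below four points, the size that the protocol itself calls clinically relevant. The Abstract's discussion says the outcomes will bear on use of the tool across the NHS, so the difference between some benefit and at least four points matters to the reader of the result.

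**Working it through.** **Inputs (protocol article).** Expected difference in mean change 5.90, SD 10.0, two-sided alpha 0.05, power 80%, 47 per group, 23% attrition (all Sample size); 1:1 allocation (Randomization); relevance threshold 4 points (Sample size and Primary objective).

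**1. Reproduce the plan's figures.**
- Expected difference: (67.9 − 61.3) − (62.8 − 62.1) = 6.6 − 0.7 = 5.9.
- Patients per group with a null of zero, normal approximation: n = 2 × [10 × (1.960 + 0.842) / 5.9]² = 45.1, rounded up to 46. The t-based solution is 46.08, rounded up to 47, as stated. Power at n = 47 is 80.8% (t-based).
- Attrition: 47 / 0.77 = 61.04, stated as 61.

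The figures reproduce with a null of zero. With a null of 4, the distance to detect would be 5.9 − 4 = 1.9, and n = 2 × [10 × (1.960 + 0.842) / 1.9]² rounds up to 435 per group (436 t-based). So the trial was not sized to test against four points.

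**2. What a significant result would show, at 47 evaluable per arm.**
- Standard error = 10 × √(2/47) = 2.063.
- 95% half-width = t(0.975, 92 df) × 2.063 = 1.986 × 2.063 = 4.10.
- Observed difference 5.9: interval 5.9 ± 4.10, about 1.8 to 10.0. Significant, but values below 4 are not excluded.
- Smallest significant observed difference: 4.10, with a lower limit at about 0.
- Observed difference needed for a lower limit of 4: 4 + 4.10 = 8.1.

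**3. How often the test is significant when the stated objective is false** (t-based, n = 47, SD 10; noncentrality = true difference / 2.063).

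| True benefit | Noncentrality | P(p < 0.05) |
|---|---|---|
| 2 points | 0.97 | 16% |
| 3 points | 1.45 | 30% |

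**4. Context only: a true benefit of exactly 4 points.** Noncentrality 4 / 2.063 = 1.94, power 48%. If all 61 per arm are evaluable, the standard error is 10 × √(2/61) = 1.811 and power is 59%.

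**5. How often the interval alone would settle the objective.** If the true difference is 5.9, the lower limit exceeds 4 with probability about 15% (noncentrality 1.9 / 2.063 = 0.92). This is not a reason to resize the trial. It shows that a claim of at least four points should not be expected from it.

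**The case against.** The best defence is that the intended hypothesis is clear from everything except one sentence. The superiority label, the plain t test, the two-sided 0.05 and the reproduced sample size all agree on a null of zero, and the Abstract speaks of the effect on activation without a margin. On this view the objective has merely absorbed the relevance threshold. Zero, 4 and 5.9 are the null, the benchmark and the expected effect, which are legitimately different quantities. Most of this stands, and it is why the remedy is to change the objective and not the test. It does not remove the mismatch, because the sentence at fault is the formal primary objective.

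It can also be said that at 47 per arm a significant observed difference must be about 4.1 or more. True, but that describes the estimate and not the true benefit, and with 61 evaluable per arm the threshold falls to 1.980 × 1.811 = 3.6.

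Three stronger readings are tempting, and the document does not support them:

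- *The trial falls short of its promised power at four points.* The Sample size section ties 80% power to 5.90 and claims none at 4. Powering for an expected effect above the relevant difference is not in itself an error.
- *The trial cannot establish a benefit of at least four points.* That is true of the p value alone. A confidence interval lying wholly at or above 4 would establish it.
- *A non-significant result will be reported as no relevant effect.* Nothing in the document says so.

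**Conclusion.** The mismatch is real and is wrong as written: the primary objective states a four-point proposition, while the analysis and the sample size address a difference from zero. Under the plan's own assumptions, a result exactly at the planned effect would be significant with an interval of about 1.8 to 10.0, and true benefits of 2 or 3 points would give significance about 16% or 30% of the time. It should be corrected, but it is a fault of wording and interpretation. The test, alpha and sample size are consistent with one another.

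The null of zero is inferred from the plain t test, the superiority wording and the reproduced 47 per group, since the article does not write it out. All figures rest on the protocol's SD of 10.0 for change and, unless stated otherwise, on 47 evaluable per arm. Better retention, or the planned increase for contamination, would narrow the interval but would not turn a test against zero into a test against four.

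**What to change.** Restate the primary objective as a superiority question: whether PAM-13 change from baseline to 3 months differs between the arms, with a null difference of zero. State that the mean difference will be reported with its 95% confidence interval and read against the four-point threshold, and that a benefit of at least four points will be claimed only if the lower limit is 4 or more.

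Optionally, add to the Sample size section that power at a true difference of four points is about 48% with 47 evaluable per arm (59% if all 61 are evaluable). This is a clarification, not a correction of the 80% figure.

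The cost is a change of wording. No patients are added, and the test and alpha do not change. The objective becomes less ambitious, and the optional sentence prints a less favourable power figure. The Trial status section reports recruitment as pending, so the change can be made through the protocol's own modification route before any outcome data exist.
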